### **C. ADDITIONAL PRINCIPLES FOR MEDICAL RESEARCH COMBINED WITH MEDICAL CARE**

31. The physician may combine medical research with medical care only to the extent that the research is justified by its potential preventive, diagnostic or therapeutic value and if the physician has good reason to believe that participation in the research study will not adversely affect the health of the patients who serve as research subjects.
32. The benefits, risks, burdens and effectiveness of a new intervention must be tested against those of the best current proven intervention, except in the following circumstances:
  - The use of placebo, or no treatment, is acceptable in studies where no current proven intervention exists; or
  - Where for compelling and scientifically sound methodological reasons the use of placebo is necessary to determine the efficacy or safety of an intervention and the patients who receive placebo or no treatment will not be subject to any risk of serious or irreversible harm. Extreme care must be taken to avoid abuse of this option.
33. At the conclusion of the study, patients entered into the study are entitled to be informed about the outcome of the study and to share any benefits that result from it, for example, access to interventions identified as beneficial in the study or to other appropriate care or benefits.
34. The physician must fully inform the patient which aspects of the care are related to the research. The refusal of a patient to participate in a study or the patient's decision to withdraw from the study must never interfere with the patient-physician relationship.
35. In the treatment of a patient, where proven interventions do not exist or have been ineffective, the physician, after seeking expert advice, with informed consent from the patient or a legally authorized representative, may use an unproven intervention if in the physician's judgement it offers hope of saving life, re-establishing health or alleviating

suffering. Where possible, this intervention should be made the object of research, designed to evaluate its safety and efficacy. In all cases, new information should be recorded and, where appropriate, made publicly available.

## ANNEX 2

### Guidance for the evaluation of the intensity of clinical signs

|                                    | Grade 1
MILD                                                                                        | Grade 2
MODERATE                                                                     | Grade 3
SEVERE                                                                                                  | Grade 4
LIFE-THREATENING                                                                                        |
|------------------------------------|----------------------------------------------------------------------------------------------------------------|-------------------------------------------------------------------------------------------------|----------------------------------------------------------------------------------------------------------------------------|----------------------------------------------------------------------------------------------------------------------------|
| Fever in the following 24h  | N/A                                                                                                            | Yes                                                                                             | N/A                                                                                                                        | N/A                                                                                                                        |
| Weakness                    | Small decrease in activity, keeps playing                                                                      | Moderate decrease in activity, has difficulty to play                                           | No activities, stopped playing                                                                                             | Lethargy                                                                                                                   |
| Muscular or articular pain* | Localised pain, weak intensity                                                                                 | Diffuse pain, weak intensity                                                                    | Real weakness; limited functions                                                                                           | N/A                                                                                                                        |
| Cephalgia*                  | Weak, not requiring treatment                                                                                  | Fluctuating, moderate, requiring treatment                                                      | Severe, responding to an initial narcotic treatment                                                                        | Refractory, requiring a repeated narcotic treatment                                                                        |
| Anorexia                    | Reduced appetite but still eating solid foods                                                                  | Reduced appetite, avoiding all solid foods                                                      | Refusing breast milk, very reduced appetite, taking neither liquids nor solids
( < 2 years ≤ 12 h;
> 2 years ≤ 24 h) | Refusing breast milk, very reduced appetite, taking neither liquids nor solids
( < 2 years ≤ 12 h;
> 2 years ≤ 24 h) |
| Nausea*                     | Small discomfort; continues to ingest normally                                                                 | Moderate discomfort; ingestion significantly reduced; certain activities are limited            | Severe discomfort; no significant ingestion, limited activities                                                            | Minimal ingestion of liquids                                                                                               |
| Vomiting                    | Transient vomiting                                                                                             | Moderate or occasional vomiting                                                                 | Orthostatic hypotension requiring an infusion                                                                              | Shock for which hospitalisation for infusion is required                                                                   |
| Abdominal pain*             | Weak                                                                                                           | Moderate, no treatment required                                                                 | Moderate to severe – treatment required                                                                                    | Severe – hospitalisation for treatment                                                                                     |
| Diarrhea                    | Transient; 3-4 liquid stools /day                                                                              | 5-7 liquid stools /day                                                                          | Orthostatic hypotension or >7 liquid stools /day or infusion required                                                      | Shock for which hospitalisation for infusion is required                                                                   |
| Cough                       | Transient, no treatment required                                                                               | Continuous, requiring a treatment                                                               | Irrepressible                                                                                                              | Cyanosis, violent cough, very difficult breathing                                                                          |
| Pruritus                    | Pruritus without rash                                                                                          | Pruritus with rash or Pruritus without eruptions disturbing the sleep                           | Moderate urticaria                                                                                                         | Severe urticaria, anaphylaxis, Quincke's Oedema                                                                            |
| Tinnitus*                   | Weak                                                                                                           | Moderate                                                                                        | Severe including hearing loss                                                                                              | N/A                                                                                                                        |
| Behavioural changes         | Minor concentration difficulties; confusion or minor agitation, normal daily activities; no treatment required | Moderate confusion or agitation; daily activities slightly impacted; minimal treatment required | Severe confusion or agitation; requiring assistance with daily activities; treatment required                              | Toxic psychosis; hospitalisation required                                                                                  |
| Flu symptoms                | Minor nasal congestion, minor rhinitis, without cough                                                          | Moderate nasal congestion, moderate rhinitis, with cough                                        | N/A
(if severe, classify the symptoms individually)                                                                     | N/A (in life-threatening circumstances, classify the symptoms individually)                                                |

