#### 5.4 Evaluation criteria

Primary evaluation criterion: The clinical safety of Eurartesim® will be evaluated through the analysis of the adverse events captured by the health agent that will contact each patient at Day 5 ( $\pm 2$  days) after starting of Eurartesim® treatment. Any AE referred (frequency, intensity, action taken, outcome) will be recorded on the specific section of the patient chart as well as those identified in the referring hospitals or through adverse events spontaneously reported by the patient detected at the health facility within 28 days after the first medication intake. Special attention will be given to the serious adverse events (SAE) and/or adverse events (AE) classified as severe and/or adverse events of special interest (AESI) (see section 8.5).

- Main secondary evaluation criteria: The cardiac and biological safety of Eurartesim® will be intensively evaluated in the nested subset of **about 1,000** patients to evaluate the effect of the administration of Eurartesim® on blood biochemistry (BUN, Creat, ALT/AST, Bilirubin, electrolytes (K+ and Cl)), full blood count (Hb, RBC, WBC and differential count)) as well as ECG parameters. In case of clinically significant abnormalities, the examination will be repeated. The occurrence of adverse events will be recorded during these visits. Concentrations of PQ will be evaluated in a subgroup of about 200 patients at baseline (Day 1 before drug administration), Day 3 (before the last drug administration and 3-4 hours after the last drug administration), and Day 7. QTc interval and piperaquine concentration relationship will also be investigated.

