### 7.2.3 Follow-up visits/contacts and clinical tolerability follow-up questionnaire

At Day 5 ( $\pm 2$  days) (after administration of the last Eurartesim® dose) following the inclusion date, the community health agent (CHA) will contact the patient at home. A further visit at the patient's home will be scheduled by the community health agent in all the cases in which the information collected during the telephone contact should be considered incomplete or unreliable ones.

He/she will then fill-in the second part of the chart (in triplicate) and report:

- His/her own 4 digit identification number (first two digits are the number of the health centre he/she is attached followed by a 2 digit number which will be assigned to him/her when the study starts).
- Date of the visit/contact.
- Clinical condition (recovered status or continuation of the illnesses).
- Compliance with the prescribed Eurartesim® treatment and in case, number of tablets of Eurartesim® not taken; an explanation of the reason why the treatment was not followed should be provided.
- Description of the symptoms experienced by the patient in case of a positive answer to the question: *“Have you noticed any unusual event/symptom since your last visit at the centre?”* Collect date of first manifestation of this/these event(s), symptom(s), intensity, treatment dis-/continuation, and evolution, in the specific section of the patient chart dedicated to the collection of Adverse Events.
- Current treatments, if taken.

In case, during his/her contact, the CHA assess that an occurred event is serious and/or severe, or detects an adverse event of special interest (see section 8.5), he/she should contact the HA and transfer the patient to the health facility in order to be examined. If necessary in the opinion of the HA, he/she should contact the investigators so that they can visit the patient and exactly define the status of the event and the causality. If the adverse event belongs to the cardiovascular category, an ECG will be performed. In addition, a thick blood smear will be prepared (for future analysis). In that event, a specific adverse event report form will be completed by the HA or the investigators.

The patient will receive first care treatment. In case any other treatment is prescribed by a HA staff or the study doctor, it will be reported on the patient chart.

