### **8.3 Definition of Adverse Event and Serious Adverse Event**

An **Adverse Event** (AE) is a sign, symptom, syndrome, disease or biological anomaly suffered by a patient or a subject participating in a clinical study and receiving a medicinal product. This term does not imply a causal relationship with the concerned treatment. Clinical signs typical of an acute malaria episode will not be considered AEs unless the healthcare personnel considers these events as exceptional due to their evolution, their seriousness, or another factor related to these events.

A **Serious Adverse Event** (SAE) is an adverse event which:

- causes death or
- is life-threatening or
- necessitates hospitalisation or prolongs hospitalisation or
- results in invalidity or long-term or significant disability or
- is a congenital defect or malformation or
- is another medically important event.

A decision on medical and scientific grounds is required to assess whether an immediate notification of an event is warranted in other situations, such as medically important events which are not life-threatening, fatal or cause hospitalization, but could endanger the patient or could rendered necessary an intervention to prevent one of the above conditions to develop.

*Remark:* Examples of such events are intensive care in the emergency room or at home to treat a bronchospasm; a haematological dyscrasia; convulsions or an asymptomatic increase ALT ( $\geq 10 \times \text{ULN}$ ) not causing hospitalisation, or the development of drug addiction or abuse.

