#### ***Serious Adverse Events***

In case of SAEs, the healthcare personnel must immediately contact the site PI / Investigator for validation of the seriousness and determination of the causality. Subsequently, the procedure described below must be followed:

- SEND (within 24 hours and fax or pdf scanned documents) the signed and dated copy of the “**Serious** Adverse Event form” and the form “SAE complementary information” to INDEPTH-Network secretariat ([contact]), Study Monitor ([contact]) and the Corporate Safety dept, Sigma-Tau via fax ([name]) or e-mail ([contact]).
- CALL immediately (the same day) the physician of the Sponsor ([contact]) responsible for safety in case of death or life-threatening events.
- CALL the local responsible person for pharmacovigilance of the project.
- The follow-up of each fatal or life-threatening AE must be provided to the Physician of the Sponsor (INDEPTH-Network), the local person responsible for the pharmacovigilance of the project and the Corporate Safety dept – Sigma-Tau within the same timeline as the initial report (within 24 hours and preferably by e-mail/fax).
- ATTACH to the chart the photocopy of all available results and examinations which were undertaken (and their date). Analysis results must be accompanied by the laboratory normal ranges. Special consideration shall be taken to ensure patient anonymity, and to the correct completion of the patient’s study specific identifier in the copies of the source documents provided to the sponsor.

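### Annex 2 defines Grade 3 and Grade 4 anorexia identically, so the two grades cannot be told apart and a longer refusal has no grade

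*Protocol*

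**What the plan says.** Annex 2 of the protocol, continued in Annex 3, is its guidance for grading the intensity of clinical signs from Grade 1 (mild) to Grade 4 (life-threatening). In the anorexia row:

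- Grade 1: "Reduced appetite but still eating solid foods".
- Grade 2: "Reduced appetite, avoiding all solid foods".
- Grade 3 (severe): "Refusing breast milk, very reduced appetite, taking neither liquids nor solids", with limits of at most 12 h below 2 years of age and at most 24 h above 2 years.
- Grade 4 (life-threatening): the same sentence with the same two limits.

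Section 5.4 makes intensity part of the primary evaluation criterion: "Any AE referred (frequency, intensity, action taken, outcome) will be recorded". Under section 7.2.3, the patient is transferred to the health facility if "the CHA assess that an occurred event is serious and/or severe". Section 8.2 sends severe events, along with serious ones and those of special interest, to the Local Pharmacovigilance Monitoring Committee.

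Seriousness is defined separately, in section 8.3, by criteria that include "is life-threatening or" and "necessitates hospitalisation or prolongs hospitalisation or". Section 8.4 has the healthcare personnel contact the site investigator "for validation of the seriousness and determination of the causality".

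**The concern.** A grading scale has to place each presentation in one grade and leave none out. The top of the anorexia row fails on both counts. Two assessors who see the same child and follow the annex exactly can record different grades, and neither is wrong. If the child refuses for longer than the stated time, the annex offers neither grade.

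Three things are at stake. The first is the consistency of a recorded component of the primary evaluation criterion across up to seven surveillance sites. The second is the severe-event trigger for longer refusals: transfer and notification depend on the event being called severe, and the annex gives no written basis for doing so. The third is a possible spill-over into expedited reporting. The Grade 4 heading uses the same word as one of the section 8.3 criteria, and under section 8.4 life-threatening events also require a same-day call to the sponsor's physician.

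The first assessor in the main cohort is usually a community health agent at the Day 5 contact, who has most need of unambiguous written guidance.

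**Working it through.** The protocol states no figure here, so the check is a comparison of text.

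**1. Grade 3 against Grade 4 anorexia.**

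| Element | Grade 3 | Grade 4 |
|---|---|---|
| Description | refusal of breast milk, liquids and solids | same |
| Limit, under 2 years | ≤ 12 h | ≤ 12 h |
| Limit, over 2 years | ≤ 24 h | ≤ 24 h |

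No element differs, and no other section of the protocol separates the two grades.

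**2. Which presentations fall where, as written.**

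- Refusal for 12 h or less under 2 years, or 24 h or less over 2 years: meets Grade 3 and Grade 4.
- Refusal beyond those limits: meets neither.
- Age exactly 2 years: no limit is given, because the bands are strictly below and strictly above 2.

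Section 6.2.1 admits patients from 6 months of age, so both age bands occur in the study.

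**3. Whether this is the table's general style.** Annex 2 has 14 rows. Four lack a usable definition in Grade 3 or Grade 4 (fever, muscular or articular pain, tinnitus, flu symptoms), leaving 14 − 4 = 10. Annex 3 has 11 rows. Four have no definition in Grade 4 (dehydration, icterus, hearing, picking up tablets), leaving 11 − 4 = 7. Of these 10 + 7 = 17 rows, 16 give different text for Grades 3 and 4. Anorexia is the only duplicate, which points to a drafting error and not to a convention.

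**4. What depends on the grade.**

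- Transfer (sections 7.1 and 7.2.3) and notification (sections 8.2, 11.1 and 11.2) depend on an event being severe or serious. Within the duration limits the event is Grade 3 or higher on either reading, so these triggers still work. Beyond the limits they have no basis in the annex.
- The incidence classes in section 9.2 are all events, serious, serious and related, special interest, leading to discontinuation, and related. None is defined by grade.
- Serious status comes from section 8.3 and investigator validation under section 8.4. The protocol does not derive it from the grade. Convulsions illustrate the separation: Annex 3 places localised or general convulsion at Grade 3, while the remark in section 8.3 names convulsions among examples of medically important events.

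**The case against.** The strongest reply is that little hangs on the split between Grades 3 and 4. Severe and serious events are handled together for transfer and committee review, no listed incidence class uses the split, and the annex is headed as guidance, without sections 8.2 to 8.5 citing it as a decision rule. All of this is correct and limits the size of the point. It does not remove it. The annex is the only guidance the protocol gives for grading intensity, intensity is part of the primary evaluation criterion, and the gap for longer refusals affects the severe-event trigger itself.

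A reader might go further and infer that neither the severity nor the serious status of anorexia can be assigned. The documents do not support that. Grades 1 and 2 are distinct, and Grade 3 or higher can be recognised within the stated limits. Seriousness is decided on the section 8.3 criteria, whatever grade is entered. What remains is narrower: the shared word life-threatening may lead someone who reads seriousness off the grade to report the same event differently.

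A reader might also want a count of affected events. The protocol gives no rate for severe anorexia. Section 8.3 also excludes signs typical of an acute malaria episode from adverse events unless staff consider them exceptional, which may keep many episodes of poor appetite out of the data. Nor does any section show that sites do in fact diverge.

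Finally, the gap for longer refusals rests on inequality signs in a table, and one could have been altered when the PDF was read. Both cells read alike and nothing in the text indicates a misreading, but a look at the printed page would settle it.

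**Conclusion.** The point holds as a drafting error with a limited but real effect. As written, Grade 3 and Grade 4 anorexia cannot be distinguished, and a refusal beyond 12 h (under 2 years) or 24 h (over 2 years) has neither grade. Anorexia intensity may therefore be graded inconsistently across sites, and the Grade 4 label may cause inconsistent reporting of serious adverse events.

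The effect covers one of the 17 rows that define both top grades. Severity in general, serious status and the planned incidence classes are not undermined. No number of affected events can be given. The conclusion assumes that the signs and limits in the available text match the printed annex. Which limits are right cannot be told from the protocol.

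**What to change.** The sponsor should compare the two anorexia cells with the source the annex cites, the WHO toxicity grading scale, and reconcile them so that Grades 3 and 4 are mutually exclusive and together cover refusals longer than the present limits. The age bands should be closed at exactly 2 years at the same time. This review does not say which limits should apply.

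A sentence in the annex stating that Grade 4 does not by itself make an event serious, and that section 8.3 decides, would remove the risk from the shared label.

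The corrected page should go to all sites with a short memo. If grading has already begun, only anorexia events recorded as Grade 3 or 4, or left ungraded, need to be re-read.

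The cost is one annex page, one site memo and a limited chart review. Sample size and planned analyses do not change.
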